### Participants

A total of 200 participants will be recruited for the study. Chinese family caregivers will be eligible to participate if they meet all of the following criteria:Chinese men or women, 21 years of age or older, able to communicate in Cantonese or Putonghua. Justifications: an ability to command the Chinese language (Cantonese or Putonghua) is essential because the acupressure protocol is written and conducted in Chinese. Furthermore, the intervention requires participants to have the self-discipline for compliance, hence the decision to select more mature participants of age ≥ 21 years.Primary caregiver of an older family member aged ≥ 65 years. Justifications: the literature has shown that caring for an older family member is a key source of caregiver stress, hence our decision to adopt a more inclusive approach to target older family members who are the care recipients, irrespective of their health problems/disabilities. We recognize that the older care recipients likely have different health problems/disabilities, which may affect their dependency on the caregivers and the level of caregiver stress. Therefore, we will take into account the care recipients’ health problems/disabilities in the data analysis.Providing unpaid care to the care recipient at no less than 14 h per week. Justification: this criterion will exclude paid or occasional caretakers whose needs and caregiver stress, if any, are likely to be different from that studied in this project.Primarily responsible for making day-to-day decisions and providing assistance to the care recipient in tasks relating to activities of daily living (e.g., bathing, dressing, and toileting) and/or instrumental activities of daily living (e.g., housework, grocery shopping, preparing meals, and managing medications). Justification: this criterion will exclude those who are not the primary caregivers.Screened positive for caregiver stress (a summed score of ≥ 25 as measured by the Caregiver Burden Inventory), with symptoms of fatigue (a mean score of ≥ 4 as measured by the Piper Fatigue Scale), insomnia (a global score of > 5 as measured by the Pittsburgh Sleep Quality Index), or depression (a total score of ≥ 10 as measured by the Patient Health Questionnaire). Justifications: caregivers with caregiver stress are the participants targeted while fatigue, insomnia, and depression are the outcome measures in the proposed study.

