### Instruments

The following study instruments (with the exception of the Demographic Questionnaire) will be administered at four time points: (a) pre-intervention (T0, baseline), i.e., on entry to study after randomization but before intervention; (b) post-training (T1, end of 2^nd^ week), i.e., on completion of the 2-weeks individual learning and practice; (c) post-intervention (T2, end of 8^th^ wk), i.e., on completion of the 8-weeks self-administered acupressure intervention; and (d) follow-up (T3, end of 12^th^ wk), i.e., 4 weeks after the completion of the intervention.The Chinese version of the Caregiver Burden Inventory (C-CBI, 24 items) [27] will be used to (i) initially screen potential participants for caregiver stress, and (ii) assess levels of caregiver stress at different time points in the study. The C-CBI has been validated for the Chinese population and demonstrated satisfactory internal consistency (Cronbach’s alpha 0.9) [27]. Each item is assessed using a 5-point Likert scale ranging from 0 (never) to 4 (nearly always). For the initial screening, participants with a summed score of ≥ 25 will be identified as experiencing caregiver stress and recruited into the study.The Chinese version of the Piper Fatigue Scale (C-PFS, 22 items) will be used to (i) initially screen potential participants for the symptom of fatigue, and (ii) assess the levels of fatigue experienced by the participant at different time points in the study. The C-PFS has been validated with good reliability (Cronbach’s alpha 0.93) [28]. Each item is assessed using a numeric scale of “0” to 10” with higher scores representing more fatigue. For the initial screening, participants with a mean score of ≥ 4 will be identified as experiencing fatigue and recruited into the study.The Chinese version of the Pittsburgh Sleep Quality Index (C-PSQI, 19 items) will be used to (i) initially screen potential participants for the symptom of insomnia, and (ii) assess the levels of insomnia experienced by the participant at different time points of the study. The C-PSQI has been validated with good reliability (Cronbach’s alpha 0.86) [29]. Insomnia (sleep disturbances in subjective sleep quality, sleep latency, sleep duration, habitual sleep efficiency, sleep disturbances, use of sleeping medication, and daytime dysfunction) will be assessed on a 4-point Likert scale ranging from 0 (no difficulty) to 3 (severe difficulty). For the initial screening, participants with a global (summed) score of > 5 will be classified as experiencing insomnia and recruited into the study.The Chinese version of the Patient Health Questionnaire (C-PHQ, nine items) will be used to (i) initially screen potential participants for the symptom of depression, and (ii) assess the levels of depression experienced by the participant at different time points of the study. The C-PHQ is one of the most popular self-administered screening tools for the symptom of depression that has been validated in the Hong Kong Chinese population [30]. Each item is scored from 0 (not at all) to 3 (nearly every day), with a total score ranging from 0 to 27. Cutoff values of 5, 10, 15, and 20 have been widely used to define mild, moderate, moderately severe, and severe depressive symptoms. For the initial screening, participants with a total score of ≥ 10 will be identified as experiencing the symptom of depression and recruited into the study.The Chinese version of the SF-12 version 2 Health Survey (C-SF-12v2, 12 items) has demonstrated validity and equivalence for Chinese populations [31] and will be used to assess health-related quality of life. The 12 items are grouped under the mental component summary and physical component summary. The survey is scored by recoding the items, computing the raw scale scores, and transforming the scores to a range from 0 to 100 according to the standard scoring algorithm. Higher scores indicate a better health status.Health economics assessment (HEA) will be assessed to determine the cost minimization [32] related to the intervention, with items on: (i) number of physician visits, (ii) use of prescription drugs, and (iii) incidence of inpatient hospitalization.A demographic questionnaire (DQ) will be used to collect information on age, education level, marital status, number and age of children, employment status, financial hardship, number of care recipients, total number of hours of caregiving per week (for the older adult care recipient and children, if appropriate), length of caring (years/months of caregiving), assistance received from other family members (including number of people providing care), paid/occasional caregivers, receipt of comprehensive social security assistance, need for financial support, and number of years living in Hong Kong. Information will also be collected regarding the care recipient’s health and dependency including age, health problems, disabilities, and degree of dependency on the caregiver.

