
### Procedures

Upon study entry, participants in both groups will be asked to complete the Chinese version of the questionnaires (T0, baseline assessment), including C-CBI for caregiver stress, C-PFS for fatigue, C-PSQI for insomnia, C-PHQ for depression, C-SF-12v2 for quality of life, HEA for cost minimization, and DQ for participant profile. The participants assigned to the intervention group will then receive the intervention as described. When the intervention group reaches post-training, post-intervention, and follow-up time points (T1, T2, and T3, respectively), participants in both groups will complete C-CBI, C-PFS, C-PSQI, C-PHQ, C-SF-12v2, and HEA. After the completion of data collection at T3, participants in the wait-list control group will then receive the self-administered acupressure training. The immediate treatment received by the intervention group, the wait-list control condition received by the control group, and the data collection points are shown in Fig. 1.

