### Data analysis

The primary outcome is caregiver stress and the secondary outcomes are symptoms of fatigue, insomnia, depression, and health-related quality of life.

The effectiveness of the self-administered acupressure intervention on caregiver stress, symptoms of fatigue, insomnia and depression, and health-related quality of life will be assessed. To do this, the scores of the C-CBI, C-PFS, C-PSQI, C-PHQ-9, SF-12v2, and HEA collected at four different time points will be analyzed for changes from baseline (T0) to the post-intervention (T2) and from the post-intervention (T2) to the follow-up (T3).

For the primary analysis, the levels of caregiver stress on completion of the intervention (T2) between the intervention and wait-list control groups will be assessed by a regression analysis with adjustment of baseline values and accounting for any possible effect of the demographics. Residuals will be checked to ensure adequacy of the method. In addition, changes in caregiver stress from baseline (T0) to follow-up (T3) will be assessed by paired *t*-tests. The intention-to-treat principle will be adopted and all study subjects will be included in the analysis with missing values replaced by the last observed values or imputed by regression substitution.

For secondary analysis, the scores of the C-PFS, C-PSQI, C-PHQ, C-SF-12v2, and HEA will be compared for differences between the intervention and wait-list control groups by a linear mixed effects model with the baseline value of the scale and the intervention group as fixed factors and the intercept as a random factor. Moreover, effects of the demographics, care recipients’ health problems/disability, and dependency on the outcomes will be explored by considering them as fixed factors in the linear mixed effects model. Changes in mean scores from baseline will also be assessed by a linear mixed effects model with the use of linear contrasts. Multivariate analysis will also be conducted to simultaneously study changes in clusters of mean scores.

Baseline characteristics (T0) between the intervention and wait-list control groups will be assessed by chi-square test and Mann–Whitney U test for categorical and continuous data, respectively.

Statistical significance is defined as *p* < 0.05 with a two-sided test. All statistical analyses will be conducted with Statistical Package for the Social Sciences (SPSS) program.

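### The week-12 (T3) analysis of caregiver stress uses paired t-tests, which make no comparison with the still-untreated wait-list arm

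*Protocol article*

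**What the plan says.** The Data analysis section sets out two analyses of the primary outcome, caregiver stress on the C-CBI.

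- At T2, "the levels of caregiver stress on completion of the intervention (T2) between the intervention and wait-list control groups will be assessed by a regression analysis". The model adjusts for the baseline score. This is a between-arm comparison.
- At T3, "changes in caregiver stress from baseline (T0) to follow-up (T3) will be assessed by paired" t-tests. No between-arm comparison of the C-CBI at T3 is named.

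The next paragraph gives the secondary outcomes a between-group mixed model: "the scores of the C-PFS, C-PSQI, C-PHQ, C-SF-12v2, and HEA will be compared for differences between the intervention and wait-list control groups". The C-CBI is not in that list.

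The Procedures section shows what data will exist. At T1, T2 and T3, "participants in both groups will complete C-CBI, C-PFS, C-PSQI, C-PHQ, C-SF-12v2, and HEA". The control arm is still untreated at T3: "After the completion of data collection at T3, participants in the wait-list control group will then receive the self-administered acupressure training". The Instruments section places T3 at the end of week 12, "4 weeks after the completion of the intervention".

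Under Participants, one entry criterion is "Screened positive for caregiver stress", defined as a summed score of 25 or more on the same inventory that serves as the primary outcome.

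**The concern.** A paired t-test sets each participant's T3 score against that participant's own T0 score. Whether it is run within each arm or on all participants pooled (the text does not say), it estimates a change over time and not a difference between randomized groups. Anything that moves scores in both arms counts towards significance: passage of time, attention from the study team, expectation, repeated completion of the questionnaire, or regression to the mean after selection on a high score.

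The wait-list arm exists to remove these influences, and at T3 it is measured and untreated. As written, the fatigue, sleep, depression and quality-of-life scales get a between-group model, while the primary outcome at T3 gets only a before-after test. At stake is whatever the trial reports on whether an effect on caregiver stress is still present four weeks after the intervention ends.

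**Working it through.** **Inputs (Sample size section):** CBI SD 17.61, mean 47.54, pre-post correlation 0.7, difference 6, type I error 5%, 83 per group before attrition, 100 planned. The two-sided test is from Data analysis and the cut-off of 25 from Participants.

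**1. The plan's own figure.** SD of change = 17.61 × √(2 × (1 − 0.7)) = 13.64. For a two-sample t-test on change scores with a difference of 6, the noncentral t gives 79.95% power at 82 per group and 80.4% at 83. So 83 is right. With 15% attrition, 83 / 0.85 = 97.6, rounded up to 98. The plan's figures reproduce, and they are for a between-group test.

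**2. Paired test in the intervention arm with no treatment effect.** Let δ be a fall common to both arms. The noncentrality is δ / (13.64 / √n) with n − 1 degrees of freedom. The standard error is 13.64 / √83 = 1.497, or 13.64 / √100 = 1.364. The two-sided critical values are 1.989 and 1.984.

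| Common fall δ (assumed) | Noncentrality, n = 83 / 100 | Significant, n = 83 | Significant, n = 100 |
|---|---|---|---|
| 0 | 0 / 0 | 5.0% | 5.0% |
| 1 | 0.67 / 0.73 | 10.1% | 11.2% |
| 2 | 1.34 / 1.47 | 26.2% | 30.6% |
| 3 | 2.00 / 2.20 | 50.8% | 58.6% |

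The protocol gives no value for δ, so the table is a range and not a forecast.

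**3. How much of δ the entry cut-off can supply.** Assume normal scores with mean 47.54 and SD 17.61 before selection. Then c = (25 − 47.54) / 17.61 = −1.28. The mean excess of selected screening scores is 17.61 × φ(c) / (1 − Φ(c)) = 17.61 × 0.1759 / 0.8997 = 3.44 points.

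- If the screening score also serves as T0, the expected fall to T3 is (1 − 0.7) × 3.44 = 1.03 points. Selection also lowers the SD of change slightly, to 13.34. The paired test is then significant in 10.7% (n = 83) to 11.9% (n = 100) of null trials.
- If T0 is a separate, later measurement that correlates r with screening, the expected fall from T0 to T3 is (r − 0.7) × 3.44, taking 0.7 as the correlation of screening with T3. At r = 0.7 this is zero, because the regression has already happened between screening and T0.

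At the cited mean, selection therefore contributes between 0 and about 1 point.

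**4. The between-arm alternative.** In a simulation of the baseline-adjusted regression (4,000 runs, 83 per arm, no treatment effect), the rejection rate was 4.8% with no common shift and 4.8% with a 3-point common shift. If the planning inputs carry over to T3, the residual SD is 17.61 × √(1 − 0.7²) = 12.58. The noncentrality for a 6-point difference is 6 / (12.58 × √(2/83)) = 3.07, which gives about 86% power, against 80.4% on change scores.

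**The case against.** The strongest reply is that the confirmatory part of the trial is sound. The primary test is a baseline-adjusted between-group regression at T2, the Aims and hypotheses section concerns the state at the end of the intervention, and the sample size rests on a between-group test. The T3 test is introduced as an addition, and no hypothesis concerns durability. All of this stands. It limits the point to the T3 analysis but does not make the paired test suitable there.

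It can also be said that a later sentence in Data analysis puts changes from baseline into a mixed model with linear contrasts. That sentence sits in the secondary-outcome paragraph, whose list omits the C-CBI, and it names no group contrast. It does not fill the gap.

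A reader might infer more than the protocol supports in four ways:

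- That the trial's primary result is compromised. It is not; the T2 comparison does not use the paired test.
- That selection on the C-CBI produces a large spurious fall. Under Recruitment, eligibility is assessed before enrolment, while Instruments places T0 after randomization, so T0 may be a separate measurement. About 1 point is then an upper value at the only mean the protocol cites. A lower source mean would give more, but none is documented.
- That the investigators will test each arm and contrast the p-values. The plan does not say so, so error rates for that procedure do not describe it.
- That the T0-to-T3 interval contradicts the T0-to-T2 and T2-to-T3 intervals named earlier in the section. The wording presents it as a further analysis, which is not a contradiction.

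**Conclusion.** The point holds for the T3 analysis of caregiver stress. The protocol names a test with no between-arm contrast where a concurrent, untreated, randomized comparison will have been measured. A significant paired result at T3 could not be attributed to acupressure.

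The size depends on a common change that the protocol does not give. With no such change the paired test keeps its 5% error rate as a test of change, but it still does not compare the arms. If selection alone acts and the screening score serves as T0, the intervention-arm test is significant in about 11–12% of null trials. Falls of 2 to 3 points, which would need time, attention or expectation effects on top, give 26% to 59%. These figures assume normal scores, the planning SD and correlation, 83 to 100 per arm and a per-arm test.

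This should be fixed. It does not threaten the T2 primary analysis, the stated hypotheses or the sample size.

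**What to change.** In Data analysis, replace the paired t-tests for caregiver stress by the baseline-adjusted between-group regression already specified for T2, applied to the C-CBI at T3. Alternatively, fit one repeated-measures model to the C-CBI at T1, T2 and T3 and report the group contrast at T3. State that this T3 comparison is supportive and that T2 remains the primary time point. Report within-arm changes from baseline descriptively, with confidence intervals and without tests.

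The cost is a change of wording before the analysis. The C-CBI is already collected in both arms at T3, so no new data, visits or participants are needed.

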### Sample size

The power calculation is based on the test for significant difference between the mean pre-post differences of the caregiver stress scores in the intervention and control groups. Because no study has used self-administered acupressure as an intervention to reduce caregiver stress, we determined our study sample size based on the findings of a previous study measuring caregiver burden of those caring for community-residing patients with Alzheimer’s disease [24]. This study reported the mean and standard deviation of the CBI score to be 47.54 and 17.61, respectively. Assuming a moderate correlation ($$ p $$ = 0.7) between the pre and post intervention CBI scores, we approximate the pooled standard deviation of a two-sample *t*-test as $$ 17.61\sqrt{2\left(1-p\right)}=13.64 $$. Taking a clinical difference of *d* = 6, which is considered a 10–15 % improvement owing to intervention (using the mean 47.54 as a reference) and a Type I error rate of 5 %, *n* = 83 was determined to have a power greater than 80 %. Assuming an attrition rate of 15 %, the target sample size is at least 98 per group. We rounded up the number of participants to 100 in each group, which makes a total of 200 participants.

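### Missing primary-outcome scores are filled by last observation or single regression substitution with no allowance for imputation uncertainty, which can shrink the effect or inflate the type I error, depending on details not fixed

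*Protocol article*

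**What the plan says.** In the protocol article, Data analysis, the primary comparison is caregiver stress (C-CBI) at T2, which "will be assessed by a regression analysis with adjustment of baseline values and accounting for any possible effect of the demographics". The same paragraph adopts intention to treat and keeps every participant in the analysis, "with missing values replaced by the last observed values or imputed by regression substitution". It does not say which method applies when, which variables enter the substitution regression, or that the variance is adjusted for filled values. The linear mixed model in the next paragraph is assigned to the secondary scales and the health economics items, not to the primary outcome.

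The Sample size section plans for missing data: "Assuming an attrition rate of" 15%. It does not divide that figure by visit or by arm.

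**The concern.** This is a stated rule for the primary outcome, not a detail left open by a condensed article. Both named methods put one value in place of each missing score, and the T2 regression would then take that value as data.

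- **Last observation.** For a missing T2 score, only T0 or T1 can be carried forward. T1 falls at the end of week 2, when training ends. Home self-practice runs from week 3 to week 8 (Intervention section). Either value therefore assumes no change over most of the intervention period.
- **Regression substitution.** A predicted value carries no residual and no estimation error. The analysis counts 200 participants when the information comes from fewer.

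At stake is either the size of the primary effect or the error rate of its test.

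**Working it through.** **Inputs from the protocol article.** SD 17.61, pre-post correlation 0.7, difference 6, 15% attrition and 100 per arm (Sample size); 5% significance level "with a two-sided test" (Data analysis).

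**Assumptions.** 15% is the share of T2 scores missing, equal in both arms and completely at random, except in step 5.

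**1. The plan's own figure.** SD of change = 17.61 × √(2 × 0.3) = 13.64. For a difference of 6, the two-sided 5% t-test has power 79.95% with 82 per group and 80.4% with 83. Then 83 / 0.85 = 97.6, so 98, rounded to 100. The sample size reproduces.

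**2. Regression substitution, arm in the imputation model.** Take the imputation regression to have the same terms as the analysis (T0 and arm). The filled values lie exactly on the fitted surface, so the estimate and the residual sum of squares equal those from the 170 observed participants. Only the counts change.
- Residual SD after baseline adjustment = 17.61 × √(1 − 0.7²) = 12.58.
- True SE = 12.58 × √(2/85) = 1.93.
- Reported SE = 12.58 × √(167/197) × √(2/100) = 1.64.
- Ratio = 1.64 / 1.93 = 0.85, so the SE is about 15% too small.
- Type I error = 2 × (1 − Φ(1.96 × 0.85)) = 9.6%.

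With missing share m the ratio is about 1 − m. Type I error is then 6.3% at 5% missing, 7.8% at 10% and 11.7% at 20%. Adding a random residual to a single fill does not cure it: the formula 2 × (1 − Φ(1.96 / √(1/(1 − m) + m))) gives 8.9% at 15%.

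**3. Regression substitution, arm left out.** Participants with the same baseline get the same filled value in both arms, so filled participants contribute no group difference: 0.85 × 6 + 0.15 × 0 = 5.1.

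**4. Last observation, equal dropout.** Baselines do not differ in expectation, so carrying T0 gives 0.85 × 6 = 5.1. If T1 is carried and a quarter of the effect is present by then (assumption), 0.85 × 6 + 0.15 × 1.5 = 5.3.

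**5. Last observation, unequal dropout with a common trend (both assumptions).** Let both arms fall by 3 points and the intervention add 6, so the true falls are 9 and 3. Carry baseline forward.
- 25% missing in intervention, 5% in control: 9 × 0.75 − 3 × 0.95 = 3.9.
- 5% missing in intervention, 25% in control: 9 × 0.95 − 3 × 0.75 = 6.3.

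With no true effect and a 5-point common drift, 25% versus 5% missing gives a bias of 5 × (0.25 − 0.05) = 1 point. Simulated type I error is then 9.1–9.5% (4,000 runs per scenario).

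**6. Simulation of steps 2 to 4** (8,000 runs, correlation 0.7 between every pair of visits, baseline-adjusted regression, 15% missing in each arm):

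| Handling of missing T2 | Type I error | Mean effect (true 6) | Power |
|---|---|---|---|
| Observed cases only | 5.2% | 6.0 | 87.8% |
| Baseline carried forward | 5.4% | 5.1 | 86.6% |
| T1 carried forward | 5.3% | 5.3 | 84.5% |
| Regression fill, arm included | 9.9% | 6.0 | not comparable (error not held at 5%) |
| Regression fill, arm omitted | 5.2% | 5.1 | 87.8% |

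The simulation agrees with the formulas. Under these assumptions, analysing only the observed scores keeps both the effect and the error rate right, and no fill does.

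**The case against.** Four objections carry weight.

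- **The error inflation is conditional.** It needs arm in the imputation regression (or separate fits by arm) and a sizeable missing share. A further strong predictor such as T1 would reduce it. A reader might infer that regression substitution as such nearly doubles the type I error. The article does not support that, because it does not name the imputation variables. Without arm, the damage is attenuation instead.
- **Carry-forward is mild when dropout is balanced.** Type I error stays at 5.3–5.4% and power at 84.5–86.6%, above the planned 80%. A reader might also infer that carry-forward always shrinks the effect. Step 5 shows that it can inflate it, and the dropout split and trend used there are not in the protocol.
- **15% is overall planned attrition.** The share missing at T2 could be lower, and the consequences would shrink with it.
- **The article is condensed.** The choice between the two methods, and the imputation covariates, may be settled in a fuller plan that is not shown. A reader might infer from the word joining the methods that the choice will be made after the data are seen. Nothing in the article says so, and the point does not depend on it.

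These limit the size of the point but do not remove it. Both methods named for the primary outcome are single imputations, and settling which applies does not supply the missing uncertainty.

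**Conclusion.** The point holds as a conditional one. Followed as written, the rule can give a wrong primary result, and which error occurs depends on details the article does not fix. With 15% of T2 scores missing, equal across arms and completely at random, there are two outcomes. Either the effect is attenuated by about 15% (carry-forward from baseline, or regression fill without arm), or the nominal 5% test runs at about 9–10% (regression fill with arm). The second is the more serious. With unequal dropout and a shared time trend, carry-forward has no predictable direction. The sample size calculation is unaffected.

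**What to change.** In Data analysis, replace the two single-imputation methods with one pre-specified method. Multiply impute missing C-CBI scores from a model that includes arm, T0, T1 and T3, and the demographics used in the primary regression. Fit the stated baseline-adjusted T2 regression in all randomized participants, and combine the results by Rubin's rules. This keeps the intention-to-treat population and the planned primary model.

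A likelihood-based repeated-measures model of the C-CBI with the T2 group contrast as the primary result would be an acceptable equivalent, but only one of the two should be named as primary. A delta-adjusted sensitivity analysis is optional.

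The cost is a change of analysis wording and a little more analysis work, with no new data or visits. The reported standard error will be larger than under regression fill: at 15% missing, between about 1.78 (12.58 × √(2/100), nothing missing) and about 1.93 (observed cases only), rather than 1.64. That increase is the uncertainty the fill leaves out. Even at the upper end, power for a 6-point difference is about 88% (observed-case simulation), above the planned 80%.

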### Aims and hypotheses

The primary aim of this randomized, wait-list controlled trial is to evaluate the effectiveness of a self-administered acupressure intervention on caregiver stress among Chinese caregivers of older family members. The secondary aim is to evaluate the effectiveness of the self-administered acupressure intervention on the Chinese family caregivers’ stress-related symptoms of fatigue, insomnia, and depression and their health-related quality of life.

We hypothesize that, on completion of a self-administered acupressure intervention, and as compared with the wait-list control group, Chinese family caregivers in the intervention group will have:(i)lower levels of caregiver stress, as measured by the Caregiver Burden Inventory;(ii)lower scores of fatigue symptoms, as measured by the Piper Fatigue Scale;(iii)lower scores of insomnia symptoms, as measured by the Pittsburgh Sleep Quality Index;(iv)lower scores of depression symptoms, as measured by the Patient Health Questionnaire; and(v)higher scores of health-related quality of life, as measured by the SF-12 Health Survey.

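### The between-group mixed model stated for the secondary outcomes has no visit or group-by-visit term, so its group coefficient averages over visits, whereas hypotheses (ii) to (v) concern the end of the intervention (T2)

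*Protocol article*

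**What the plan says.** The Aims and hypotheses section places all five hypotheses at one time and makes them between-group: "on completion of a self-administered acupressure intervention, and as compared with the wait-list control group". Hypotheses (ii) to (v) cover fatigue, insomnia, depression and health-related quality of life.

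The Instruments section says that the scales "will be administered at four time points". T1, at the end of week 2, is "on completion of the 2-weeks individual learning and practice". T2, at the end of week 8, is "on completion of the 8-weeks self-administered acupressure intervention". T3 follows 4 weeks later. Under Procedures, at T1, T2 and T3 "participants in both groups will complete C-CBI, C-PFS, C-PSQI, C-PHQ, C-SF-12v2, and HEA".

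Under Data analysis, the secondary paragraph covers the four secondary scales and the health economics items. It sets one arm against the other on each of them in a mixed model, whose terms it gives as follows: "with the baseline value of the scale and the intervention group as fixed factors and the intercept as a random factor". The further fixed factors to be explored are demographics and the care recipient's health problems, disability and dependency. Visit is not among them.

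Two other sentences in that section bear on timing. A general one says that the scores "will be analyzed for changes from baseline (T0) to the post-intervention (T2) and from the post-intervention (T2) to the follow-up (T3"). A later one adds that change in mean scores from baseline will also be assessed by a mixed model with linear contrasts. Neither names a comparison between groups at T2. For the primary outcome alone, the section does state a baseline-adjusted regression comparing the groups at T2.

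**The concern.** The secondary model is listed term by term, so it can be judged as written. It has one group coefficient and nothing that lets the group difference vary by visit. The design gives reason to expect that it may vary: T1 comes after training but before the six weeks of twice-daily self-practice, and T3 comes four weeks after the intervention ends.

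At stake is whether the reported estimate and p-value for four of the five hypotheses refer to the time point that those hypotheses name. If benefit builds up with practice or fades afterwards, the averaged coefficient understates the T2 effect. If it is constant, the average is a fair and more precise estimate. The plan does not say which quantity it wants. With no T2 contrast named, the choice among several mixed-model results stays open until the data are in.

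**Working it through.** **1. The plan's own figure.** The only quantitative assumptions are in the Sample size section and concern the CBI: SD 17.61, pre-post correlation 0.7, difference 6, two-sided 5%.
- SD of change = 17.61 × √(2 × (1 − 0.7)) = 13.64.
- n per group = 2 × (1.96 + 0.8416)² × 13.64² / 6² = 81.1, so 82. The t-test version gives 82.1, so 83.
- Power at 83 per group is 0.80 to 0.81, and 83 / 0.85 = 97.6, so 98.

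The stated 83 and 98 reproduce. They concern the primary outcome and are not affected by this point.

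**2. Which visits can enter.** The Data analysis section does not say.
- If only T2 entered, each person would have one score, and a random intercept could not be separated from the residual. The random intercept therefore implies at least two post-baseline scores.
- The schedule offers T1, T2 and T3. The changes named in the general sentence involve T0, T2 and T3. Both readings, T1 to T3 and T2 with T3, are carried below.

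**3. What the group coefficient estimates.** With complete data, a random-intercept model with baseline and group only gives the baseline-adjusted group difference in person means. For k visits this is the unweighted mean of the k visit effects.

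Mean of visit effects as a share of the T2 effect, T1 to T3 entered (profiles assumed):

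| Effect at T1, T2, T3 (T2 = 1) | Share |
|---|---|
| 1, 1, 1 | 1.00 |
| 0, 1, 1 | 0.67 |
| 0.25, 1, 0.75 | 0.67 |
| 0.25, 1, 0.5 | 0.58 |
| 0, 1, 0.5 | 0.50 |
| 0, 1, 0 | 0.33 |

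Simulation (4,000 per group, all correlations 0.7) gave 0.97, 0.69, 0.75, 0.56, 0.50 and 0.33 for the stated model. With visit and group-by-visit added, the T2 contrast gave 0.96 to 1.08 of the T2 effect throughout.

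**4. Illustrative power.** The documents give no effect size, SD or correlation for the secondary scales, so the CBI values are borrowed as an assumption. T2 effect = 6 / 17.61 = 0.34 SD; correlation 0.7 between all visits; 100 per arm; no attrition.

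Baseline-adjusted variance of a mean of k visits, in SD² units: v = (1 + (k − 1) × 0.7) / k − 0.7². SE = √(2v / 100). Power = Φ(effect / SE − 1.96).
- k = 1: v = 1 − 0.49 = 0.51, SE = 0.101
- k = 2: v = 0.85 − 0.49 = 0.36, SE = 0.085
- k = 3: v = 0.80 − 0.49 = 0.31, SE = 0.079

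| Analysis | Assumed effects (SD) | Estimate | Power |
|---|---|---|---|
| T2 contrast | 0.34 at T2 | 0.34 | 92% |
| Stated model, T1 to T3 | 0, 0.34, 0.17 | 0.17 | 58% |
| Stated model, T1 to T3 | 0, 0.34, 0 | 0.11 | 30% |
| Stated model, T2 and T3 | 0.34, 0.17 | 0.255 | 85% |
| Stated model, T1 to T3 | 0.34 at each | 0.34 | 99% |

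At 83 per arm, the size left after the planned attrition, the T2 contrast has 87%. The averaged test over T1 to T3 has 50% for effects 0, 0.34, 0.17 and 98% for a constant effect.

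**The case against.** The best defence is that time-specific analysis is clearly intended. The section names the T0 to T2 and T2 to T3 changes for all scales, and contrasts for change over visits imply that visit is a factor in some model. This is a condensed article, and full mixed-model terms are commonly left to an analysis plan. Much of this stands: the plan is under-described rather than firmly committed to a time-averaged test. It does not remove the point, because the one model stated for comparing groups is spelled out without visit, and the sentences on changes do not say that they compare groups at T2.

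Some stronger readings are tempting but not supported:
- A reader might infer that the plan commits to averaging T1, T2 and T3. The text never says that T1 enters. If only T2 and T3 do, the illustrative estimate rises from 50% to 75% of the T2 effect.
- A reader might infer that the contrasts use baseline as both covariate and response, or cannot be formed at all. The sentence on contrasts says that they are an additional assessment and can describe a separate model, so this is not shown.
- A reader might fear that time trends leak into the group effect through unequal dropout. The primary paragraph includes all subjects with missing values carried forward or imputed. If that also covers the secondary scales, visits are balanced and an omitted common visit effect does not shift the group estimate.
- A zero effect at T1 is an assumption. By then participants have had four training sessions, each with 30 minutes of guided practice.

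**Conclusion.** The point holds as a mismatch between the quantity estimated and the hypothesis. The stated between-group model for the secondary outcomes yields an average over whichever post-baseline visits enter, and no between-group T2 test is named for hypotheses (ii) to (v).

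Its size depends on effect profiles that the documents do not give. Where the effect is weaker at T1 or T3, the assumed profiles over T1 to T3 put the estimate at 33% to 67% of the T2 effect. A constant effect gives no bias and more power. It would therefore be wrong to conclude that the stated model always loses power. Nor does averaging make the test invalid when there is no effect at any visit.

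Severity is moderate. The primary outcome already has a baseline-adjusted comparison at T2 and is unaffected, as is the sample size.

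**What to change.** In the secondary paragraph of Data analysis:
- state which post-baseline visits enter the mixed model;
- add visit (categorical) and group-by-visit as fixed factors beside baseline and group;
- name the T2 group contrast as the test of hypotheses (ii) to (v), with contrasts at other visits supportive;
- say whether the linear contrasts for change from baseline come from this model or a separate one, and whether they compare groups.

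Baseline-by-visit terms and an unstructured within-person covariance are optional refinements.

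The cost is wording only, with no new data, visits or participants. The one statistical price is some power if the effect really is constant over visits: in the illustration, about 92% for the T2 contrast against 99% for the average over T1 to T3. If the average over visits is in fact what is wanted, the alternative is to restate hypotheses (ii) to (v) to say so before the data are seen.
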